## Abstract

**Background:**

Lifestyle risk factors, in particular smoking, nutrition, alcohol consumption and physical inactivity (SNAP) are the main behavioural risk factors for chronic disease. Primary health care (PHC) has been shown to be an effective setting to address lifestyle risk factors at the individual level. However much of the focus of research to date has been in general practice. Relatively little attention has been paid to the role of nurses working in the PHC setting. Community health nurses are well placed to provide lifestyle intervention as they often see clients in their own homes over an extended period of time, providing the opportunity to offer intervention and enhance motivation through repeated contacts. The overall aim of this study is to evaluate the impact of a brief lifestyle intervention delivered by community nurses in routine practice on changes in clients' SNAP risk factors.

**Methods/Design:**

The trial uses a quasi-experimental design involving four generalist community nursing services in NSW Australia. Services have been randomly allocated to an 'early intervention' group or 'late intervention' (comparison) group. 'Early intervention' sites are provided with training and support for nurses in identifying and offering brief lifestyle intervention for clients during routine consultations. 'Late intervention site' provide usual care and will be offered the study intervention following the final data collection point. A total of 720 generalist community nursing clients will be recruited at the time of referral from participating sites. Data collection consists of 1) telephone surveys with clients at baseline, three months and six months to examine change in SNAP risk factors and readiness to change 2) nurse survey at baseline, six and 12 months to examine changes in nurse confidence, attitudes and practices in the assessment and management of SNAP risk factors 3) semi-structured interviews/focus with nurses, managers and clients in 'early intervention' sites to explore the feasibility, acceptability and sustainability of the intervention.

**Discussion:**

The study will provide evidence about the effectiveness and feasibility of brief lifestyle interventions delivered by generalist community nurses as part of routine practice. This will inform future community nursing practice and PHC policy.

**Trial Registration:**

ACTRN12609001081202

## Background

Smoking, nutrition, alcohol consumption and physical activity (SNAP) are the main lifestyle risk factors for chronic disease and a major cause of morbidity, mortality and impaired functioning [1,2]. In Australia, over 90% of adults do not consume the recommended five serves of vegetables per day, over half do not consume adequate amounts of fruit and 62% are overweight or obese [3]. Approximately one third of adults are classified as physically inactive, one in five (20%) smoke and of the 59% of the population who drink alcohol, 21% do so at a level which would pose a risk to their health [3]. The four SNAP risk factors have been shown to predict a fourfold difference in mortality, equivalent to 14 years in chronological age [4]. In terms of morbidity, the World Health Organization estimates that 80% of cardiovascular disease, 90% of type 2 diabetes and 30% of all cancers could be prevented if lifestyle risk factors were eliminated [1].

Primary health care (PHC) has been identified as a suitable setting to provide individual intervention for lifestyle risk factors because of the accessibility, continuity, and comprehensiveness of the care provided [5]. Evidence also suggests that brief lifestyle interventions delivered in PHC are effective for smoking cessation [6] and 'at-risk alcohol' consumption [7], while moderate to high intensity interventions have shown promise for improving weight, diet and physical activity levels in high risk patients in PHC [8-12].

Within the context of PHC, general practitioners have been the main targets to deliver lifestyle interventions to patients, but relatively little attention has been paid to the role of nurses working in the PHC setting, in particular community health nurses. In Australia, generalist community nurses (GCN) are uniquely placed to provide individual lifestyle intervention because they: 1) frequently see patient with existing chronic conditions that may benefit from lifestyle change; 2) often have ongoing contact with patients over an extended period of time, providing the opportunity to offer intervention and foster motivation through repeated contacts; 3) mainly see clients in their own home providing opportunity for observation of the living situation and intervention with the wider family/carers; 4) may reach disadvantaged individuals and other segments of the population who have poor contact with GPs. Furthermore, our previous research has shown that community health nurses consider the provision of lifestyle intervention an appropriate component of their role as it fits well with their philosophy of providing holistic care, is often relevant to the clients presenting issue and is well accepted by clients [13].

While the health education and promotion role of community nurses is well recognised [13-17], few studies have evaluated the effectiveness of lifestyle interventions provided by community nurses in routine practice. A study in the USA reported that patients who received smoking cessation counselling from a home health care nurse were twice as likely to be continuously abstinent at 12 months compared to those receiving usual nursing care [18]. Community nursing follow up has also been shown to be effective in promoting abstinence and retention rates in outpatient treatment of alcohol dependent patients [19]. While these findings are promising, we are unaware of previous studies that have examined the effectiveness of community nurses delivering intervention across all four lifestyle risk factors in routine practice.

### Study Aim, Objectives and Hypotheses

The overall aim of this study is to evaluate the impact of a brief lifestyle intervention delivered by GCNs in routine practice on changes in clients' SNAP risk factors.

The study has three main objectives:

1. To develop an intervention to facilitate GCNs to undertake lifestyle screening and brief intervention during routine consultations and to promote referral of 'at-risk' clients to available private and public services;

2. To evaluate the impact of these interventions on change in clients' lifestyle risk factors and related mediators (eg stages of change);

3. To describe the indicative costs and resources utilised by the community nurse services in delivering the intervention.

It is hypothesised that:

1. 20% more clients who are at high risk (defined as having at least one lifestyle risk factor) in the intervention group will be offered evidence-based interventions to modify their risk factors compared with clients in the comparison group.

2. Clients in the intervention group will be significantly more likely to progress in their stage of change compared to comparison clients.

3. Clients in the intervention group will have a reduction in their lifestyle risk factor scores compared to clients in the comparison group.

## Methods/Design

### Study Design and Setting

This quasi-experimental study is being conducted in GCN services in the state of NSW, Australia. Within Australia, GCNs can be either registered or enrolled nurses who perform a diversity of roles depending on the service in which they work. The role has traditionally focused on providing a range of nursing care in people's homes such as assisting with activities of daily living, wound management, chronic disease care, continence management, palliative care, medication management, disability and dementia care. Coordination of care with other service providers and health promotion has also traditionally been a major part of their role.

A quasi-experimental design was chosen because it was not feasible to randomise the intervention according to individual patient or practitioners within the services. GCN services have been randomly allocated to an 'early intervention' group or 'late intervention' (comparison) group. 'Early intervention' services are provided with training and support for nurses in identifying and offering brief SNAP intervention for clients during routine consultations (see service-level intervention). Data is being collected from clients in both groups at baseline, three months and six months to examine short and medium term change in SNAP risk factors. This will enable a comparison of client outcomes between early and late intervention groups. After the six month data collection point the 'late intervention' group will be offered the same training and support as the early intervention group.

### Power and Sample Size Calculation

The sample size calculation is based on the primary outcomes of change in continuous self reported measures of lifestyle risk factors rather than differences in proportion of individuals in each risk category (secondary outcomes). There is evidence that risk associated with diet, physical activity and weight is continuous [20-22]. Achieving a shift in risk categories is more difficult to demonstrate in the context of a brief intervention and would require a very large sample size which is beyond the scope and resources of this trial. Hence the focus is on change in continuous measures of lifestyle risk factors as the primary outcomes.

A sample size of 360 clients in each group (total n = 720) is required to have 80% of power to detect the following difference between intervention and comparison groups:

▪ Mean difference of 1 serve of fruit and vegetables consumed (equivalent to 22% increase in the 'early intervention' group);

▪ Mean difference of 1.2 for physical activity scores as measured by a validated brief physical activity assessment tool [23] (equivalent to a 29% increase in mean scores in the 'early intervention' group);

▪ Mean difference of 0.6 for alcohol risk scores as measured by the AUDIT-C tool [24] (equivalent to a 10% reduction in mean scores in the 'early intervention' group);

▪ Mean difference of 4.1 kg in self reported weight (equivalent to a 4.4% weight reduction in the 'early intervention' group).

This is based on 5% significance level and 80% power (β = 0.8 and α = 0.05) allowing 20% lost to follow-up and a design effect of 1.8 due to clustering. The expected differences between intervention and comparison groups has been estimated based on previous research [25]. These differences are also considered meaningful from a population health perspective. Baseline prevalence of risk factors is based on NSW Health Survey 2006 for individuals aged 45-74 years [26].

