### Recruitment

#### Generalist Community Nursing Services

Four GCN services were recruited to participate in the trial. An expression of interest to participate in the trial was sent out to all seven Area Health Services(AHS) in NSW. In NSW, AHS are responsible for providing all hospital-and community-based health care apart from general practice and PHC services for specific population groups such as Aboriginal and Torres Strait Islanders. AHS were asked to nominate suitable GCN services which were ranked and selected according to the selection criteria provided in Table 1.

**Table 1 T1:** Selection criteria for recruiting generalist community nursing services to participate in the trial

Types	Selection Criteria
**Inclusion Criteria**	The team deliver GCN services to clients between 30 and 80 years of age The team is able to recruit sufficient numbers of eligible clients into the study in a given recruitment period (based on trial sample size calculation). The individual clinicians are interested in participating and commit to undertaking training and intervention Willingness of the service to accommodate a recruitment officer to work on site to identify and contact potentially eligible clients from client referrals. Willingness of the service to review and modify service assessment protocols to include standard tools for identification SNAP risk factors (if not already included). The team/services has the capacity to participate in SNAP training The team/service has the capacity to deliver SNAP intervention to a given number of clients in a given intervention period. The team/service is broadly representative of community nursing services statewide (choosing 'typical service(s)'). Willingness of the service to participate in project management meetings with study management team body to support the trial implementation (eg service manager and AHS project/recruitment officer).

**Exclusion Criteria:**	Teams/services undergoing concurrent changes in management, structure or service deliver that would impact on capacity to be involved in the trial. Involvement in other service development activities that may contaminant trial activities (eg concurrently delivering self management program for clients).

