#### Recruitment of Clients

In order to reach the required sample size, GCN services are required to recruit 180 clients each. Clients referred to participating GCN services meeting the selection criteria (Table 2) are invited to participate in the study. Potential participants are contacted by phone on the day of referral (where ever possible) by a trained local recruitment officer. Clients who consent to take part in the study then participate in a telephone interview to collect baseline data (see data collection). A total of 720 clients (average 180 clients per service) will be recruited at baseline. We expect a 20% loss to follow-up of clients of over the study period, leaving 576 clients (or 288 in each group).

**Table 2 T2:** Selection criteria for recruiting clients to participate in the trial

Types	Selection criteria
**Inclusion criteria**	Clients referred to community nursing services Age 30-80 years Able to read and understand English at a level that enables the client to participate in a telephone administered survey and to understand the participant information sheet.

**Exclusion criteria**	Palliative care clients Clients receiving one off visit or service Clients with significant cognitive impairment (unable to complete telephone administer survey). Clients who are currently receiving help in changing their lifestyle from a health professional (other than their GP) such as a dietitian or exercise physiologist Clients who are currently attending a chronic disease management program such as cardiac rehabilitation, diabetes education program etc. Clients who have attended the generalist community nursing service in the previous six months (and therefore may have already received lifestyle intervention)

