### Randomisation and Blinding

Services were randomly allocated to an 'early intervention' or 'late intervention' (comparison) group. Randomisations were performed by a person independent of the research team. Staff involved in the client data collection are independent of those involved in the intervention and blind to which services were randomised to intervention or comparison groups.

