### Late Intervention (comparison) group

Two of the four GCN services have been randomly allocated to the 'late intervention' condition. These services will not receive the study intervention till after the six month data collection point and continue to deliver 'usual care'. This will enable the effectiveness of the service and client level intervention to be assessed in comparison to usual practice.

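### The stated 80% power makes no allowance for having only two services per arm; on 2 degrees of freedom the same signal has about 35% power

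*Protocol article*

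**What the plan says.** Under Power and Sample Size Calculation the protocol article says "A sample size of 360 clients in each group (total n = 720) is required to have 80% of power" for four listed mean differences: 1 serve of fruit and vegetables, 1.2 physical activity points, 0.6 AUDIT-C points and 4.1 kg. The basis is given as "This is based on 5% significance level and 80% power (β = 0.8 and α = 0.05". (Labelling 0.8 as β is a slip of notation and has no bearing here.) Only two allowances are listed: "allowing 20% lost to follow-up and a design effect of 1.8 due to clustering". No standard deviations, sidedness, critical values or clustering unit are given.

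The design is stated elsewhere in the article:
- Generalist Community Nursing Services: "Four GCN services were recruited to participate in the trial".
- Randomisation and Blinding: "Services were randomly allocated to an 'early intervention' or 'late intervention' (comparison) group".
- Late Intervention (comparison) group: "Two of the four GCN services have been randomly allocated to the 'late intervention' condition".
- Recruitment of Clients: "GCN services are required to recruit 180 clients each", and "We expect a 20% loss to follow-up of clients of over the study period, leaving 576 clients (or 288 in each group".

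Under Statistical Analysis, Client Outcomes, the article mentions regression for clustered data or multilevel models. The only levels it names are repeated measures within clients.

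**The concern.** When whole services are allocated, the arm effect has to be judged against variation between services. With four services and two arms, that variation is estimated on 4 − 2 = 2 degrees of freedom, and the two-sided 5% critical value is 4.30 instead of 1.96. Multiplying a sample size by a design effect does not bring this in.

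The stated power is what a reader uses to judge what a non-significant result would mean. If the true chance of detection is nearer one in three than four in five, such a result says much less than the article implies. Recruiting more clients in the same four services would not restore 80%.

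**Working it through.** **Inputs.** From the article: 360 recruited per arm, 20% loss, design effect 1.8, α = 0.05, 80% power, four services (two per arm), 180 recruited per service. Assumed, because the article does not say: a two-sided test, a design effect that refers to services, and 80% power calculated by the large-sample normal formula.

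**1. The article's own figures.**
- Completers per arm: 360 × 0.8 = 288, and 576 in total, as stated.
- Completers per service: 288 / 2 = 144.
- Effective sample size per arm: 288 / 1.8 = 160.
- Without standard deviations, 360 cannot be rebuilt independently. It can be inverted. 80% power corresponds to a signal-to-noise ratio (non-centrality) of 1.960 + 0.842 = 2.80, and so to a standardised difference of 2.80 × √(2/160) = 0.313. Putting 0.313 and 160 per arm back into the normal formula returns 80%.

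**2. Implied ICC.** From design effect = 1 + (m − 1) × ICC:
- m = 144: 0.8 / 143 = 0.0056.
- m = 180: 0.8 / 179 = 0.0045.

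**3. The same signal on 2 degrees of freedom.** Non-central t, 2 degrees of freedom, non-centrality 2.80, critical value 4.303: power = 35.2%. A simulation of t-tests on two versus two service means (400,000 replicates) gave 35.1%. The missing standard deviations do not matter for this step, because the claimed 80% already fixes the non-centrality. The design effect is included in full.

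**4. Sensitivity to the assumptions.** The standardised difference is held at 0.313 and 144 completers per service are used, except in the one-sided row.

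| Case | Design effect | Non-centrality | Power on 2 df |
|---|---|---|---|
| 1.8 set at 144 per service (ICC 0.0056) | 1.80 | 2.80 | 35% |
| 1.8 set at 180 per service (ICC 0.0045) | 1 + 143 × 0.00447 = 1.64 | 2.80 × √(1.8/1.64) = 2.94 | 38% |
| Whole calculation one-sided 5% | 1.80 | 1.645 + 0.842 = 2.49 | 50% |
| Assumed ICC 0.01 | 1 + 143 × 0.01 = 2.43 | 2.80 × √(1.8/2.43) = 2.41 | 28% |
| Assumed ICC 0.02 | 1 + 143 × 0.02 = 3.86 | 2.80 × √(1.8/3.86) = 1.91 | 20% |

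The last two ICCs are illustrations. The article gives none.

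**5. What 80% would take.** On 2 degrees of freedom, 80% power needs a non-centrality of about 5.65, and 5.65 / 2.80 = 2.02. With unlimited clients in each of the four services, the non-centrality tends to 0.313 / √ICC. That is 4.19 at ICC 0.0056 (power 60%) and 4.69 at ICC 0.0045 (power 67%).

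**6. If service is left out of the model.** Client-level degrees of freedom keep nominal power near 80%, but for a simple cross-sectional comparison at design effect 1.8 the two-sided type I error becomes 2 × [1 − Φ(1.96/√1.8)] = 14% instead of 5%. So this route does not give a valid 80% either.

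**The case against.** The strongest reply is that the article shows neither formula nor critical values. Normal critical values, a two-sided test and a service-level design effect are therefore inferred, and the 1.8 might describe clustering by nurse. That stands as a limit on the exact figure. It does not rescue the 80%: the only allowances listed are attrition and the design effect, nothing points to a correction for few services, and service remains the randomised unit whatever the 1.8 describes.

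A second reply is that the 35% belongs to a test the article does not clearly specify, since the named model levels omit service. This also stands, and the fix has to deal with it.

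Third, more clients per service would help to some extent, because within-service sampling is still 1/1.8 = 56% of the variance. That is true, but power stops at 60% to 67%.

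A reader might infer more than the article supports:
- **That each of the four listed differences has 35% power and must simply be doubled.** This needs all four outcomes to share the standardised difference 0.313. One sample size is quoted for four outcomes without standard deviations. If the most demanding outcome set it, the others have more than 35%.
- **That the implied ICC is too favourable or unsupported.** This needs an outside benchmark, and an article may leave the source of a design effect to the full protocol.
- **That a null result will be reported as an adequately powered negative.** Nothing in the article says so.

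**Conclusion.** The point holds. The article claims 80% power for a design that, with two randomised services per arm, does not deliver it. Under the three assumptions listed in the working, power is about 35%. The plausible alternative readings of the article's own inputs give 38% to 50%, and a higher ICC lowers the figure. None of the readings examined restores 80%. The direction is secure. The exact percentage is conditional, and it describes an analysis that respects service as the unit of allocation. For an effect whose nominal power is exactly 80%, the detectable size roughly doubles; the documents do not allow that to be carried over to each listed outcome.

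**What to change.** Keep n = 720. Under Power and Sample Size Calculation:
- Replace the 80% with the power on 2 degrees of freedom: about 35%, or the matching figure if the calculation was one-sided or the 1.8 was set at 180 per service.
- State the sidedness, that the design effect refers to services, and the implied ICC (0.0056 at 144 completers, 0.0045 at 180 recruited). Note that a larger ICC lowers power, for example to about 28% at 0.01 and 20% at 0.02.
- Say that the figure applies to an analysis that includes service as the unit of allocation, and reconcile this with Statistical Analysis, Client Outcomes, which names only repeated measures within clients.
- Have the sponsor recalculate the detectable difference for each outcome from the standard deviations actually used, not by doubling all four.
- Do not describe the effectiveness comparison as having 80% power.

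The cost is a change of text and a recalculation. No further clients are needed, and the services already allocated are unaffected. The downside is that the stated power becomes less favourable.
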